## Abstract

**Background:**

The limited available data suggest that the prevalence of problem gambling is increased among young adults with first-episode psychosis, possibly due in part to several risk factors for problem gambling that are common in this population. Aripiprazole, a widely used antipsychotic drug, has also been linked to cases of problem gambling, but causality remains uncertain. Although the consequences of problem gambling further hinder the recovery of people with first-episode psychosis, there is a paucity of research about this comorbidity and its risk factors. Additionally, to our knowledge, no screening instrument for problem gambling tailored to these individuals exists, contributing to its under-recognition. Further, treatment approaches for problem gambling adapted to this population are at an embryonic stage, while existing treatments effectiveness remains to be documented. Using an innovative screening and assessment procedure for problem gambling, this study aims to identify risk factors for problem gambling among people with first-episode psychosis and to document the effectiveness of standard treatment approaches.

**Methods:**

This is a multicenter prospective cohort study conducted in two first-episode psychosis clinics, including all patients admitted between November 1st, 2019, and November 1st, 2023, followed for up to 3 years until May 1st, 2024. These 2 clinics admit approximately 200 patients annually, for an expected sample size of 800 individuals. The primary outcome is the occurrence of a DSM-5 diagnosis of gambling disorder. All patients are screened and evaluated for problem gambling using a systematic procedure at admission, and every 6 months thereafter. Socio-demographic and clinical variables are prospectively extracted from the patients’ medical records. The nature and effectiveness of treatments for problem gambling offered to affected individuals are also documented from medical records. Survival analyses with Cox regression models will be used to identify potential risk factors for problem gambling. Descriptive statistics will document the effectiveness of treatments for problem gambling in this population.

**Discussion:**

A better understanding of potential risk factors for problem gambling among people with first-episode psychosis will allow for better prevention and detection of this neglected comorbidity. Results of this study will also hopefully raise clinicians’ and researchers’ awareness and serve as the basis to adapted treatments that will better support recovery.

**Trial registration:**

ClinicalTrials.gov, NCT05686772. Retrospectively registered, 9 January 2023.

## Background

There is no denying that gambling is a popular activity, with about 2 in 3 adults reporting some type of gambling in 2018, in Canada [1]. While most of these people only gamble occasionally, 0.12–5.8% of the global population has problem gambling (PBG) [2], which can be defined as a gambling behavior that causes harmful consequences for the person, his social network and community [3]. PBG frequently co-occurs with other mental health disorders, including mood and anxiety disorders, as well as substance use and personality disorders [4]. There is also evidence to suggest that the prevalence of PBG may be up to 4 times higher in people with psychotic disorders compared to the general population [5–7]. This proportion seems to be even greater among young people with first-episode psychosis (FEP), as suggested by the only study to date examining PBG among this population [8]. In this study, the prevalence of PBG of 6.4% among 219 patients was found to be 16 times higher than the 0.4% found in the general population [9]. In addition to a possible sharing of genetic influences between psychotic disorders and PBG [10], this comorbidity may also be due in part to several risk factors for PBG that are common among people with FEP, including an over-representation of males, young age, frequent psychiatric comorbidities, such as substance use disorders and personality disorders, as well as low socioeconomic status and homelessness [11]. While these risk factors have mostly been documented in general population samples, there is a paucity of data specific to individuals with psychotic disorders. Furthermore, there also appeared to be an association between the occurrence of PBG and aripiprazole, a widely used antipsychotic drug for the treatment of FEP, which had already been reported in previous case reports [12, 13]. Indeed, among the 14 FEP patients who developed PBG, 12 cases occurred during aripiprazole treatment, resulting in an adjusted odds ratio of 8.6 (*p*-value = 0.012). However, the retrospective design of this study, preventing the assessment of a potential causal link, and the limited existing literature do not allow firm conclusions to be drawn about this possible association [8]. Furthermore, there was no systematic screening for PBG at the study site at that time, which may have led to detection and monitoring bias.

The consequences of PBG are manifold and include financial hardship, broken social relationships and isolation, psychological distress and an increased risk of suicide [14, 15]. Although data regarding the consequences of PBG among individuals with a psychotic disorder are scarce, these can certainly be hypothesized as being all the more amplified [16–18]. Indeed, psychotic disorders are associated with several repercussions that can be exacerbated by the concomitant presence of PBG, including an increased rate of suicide and violent acts, stigma, low employment rates, and a 15-to-20-year decrease in life expectancy [19–21]. Not surprisingly, treatment of psychiatric comorbidities, which are common in people with a psychotic disorder, is critical to recovery [22, 23]. Despite this, to our knowledge, there are no tools to screen for PBG specifically tailored to this population, while approaches to treating PBG comorbid to a psychotic disorder are virtually non-existent [24–26]. Findings generated by these unmet needs is a low rate of PBG screening among people with a psychotic disorder by healthcare professionals and suboptimal treatment, hindering their hope for recovery [27–30].

Using an innovative screening and assessment procedure for PBG tailored to young adults with FEP, the main aim of this study is to test the hypothesis that risk factors for PBG in this population include substance use disorders, personality disorders, and the use of aripiprazole or other antipsychotics sharing the same mechanism of action (i.e., partial dopamine agonism). It also aims to demonstrate that current treatments for PBG, which have not been adapted for people with FEP, are currently insufficient to lead to recovery.

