### Independent variables

Variables that will be prospectively extracted from the patients’ medical records include socio-demographic (sex at birth, gender identity, ethnicity, employment status, education level, relationship status, living arrangements, criminal history) and clinical variables (main DSM-5 psychiatric diagnosis, psychotic illness severity as rated by the treating psychiatrist using the Clinical Global Impressions Severity scale, comorbid DSM-5 psychiatric diagnoses, community treatment order, medication treatment, including antipsychotics and all other psychotropic drugs [i.e., antidepressants, benzodiazepines, hypnotics, mood stabilizers, psychostimulants]). Regarding medication, information on both current (i.e., during the follow-up period) and past (i.e., prior to admission in the clinics) drugs will be collected (including dosages, frequency, and route of administration). A patient will be considered exposed to a drug after receiving it for greater than 1 month (or 1 injection in the case of long-acting injectable antipsychotics). Medications administered on an as-needed basis will not be considered. Gambling history (i.e., prior to patients’ admission in the clinics) will be questioned by the case managers as part of the screening procedure for PBG and divided in 3 categories, i.e., none, occasional/recreational, or PBG (i.e., DSM-3 or DSM-4 diagnosis of pathological gambling or DSM-5 diagnosis of gambling disorder). For patients with PBG and/or gambling disorder, the nature of the treatments received for their gambling problematic as well as their effectiveness in resolving it will be documented.

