### Statistical analyses

Patients’ socio-demographic and clinical characteristics will be detailed using descriptive statistics. Survival analyses using Cox regression models will be performed to identify potential risk factors for both primary and secondary outcomes. Potential risk factors that will be examined include sex at birth, gender identity, ethnicity, employment and relationship status, criminal history, psychiatric comorbidities (i.e., substance-use disorder, personality disorder), the use of aripiprazole, the use of dopamine partial agonists other than aripiprazole (i.e., brexpiprazole, cariprazine) and the use of any dopamine partial agonists. Cox regression models will be constructed for each of these variables to adjust for potential confounding factors identified using the directed acyclic graph approach. In order to detect a hazard ratio greater than 4 between the use of aripiprazole and the primary outcome with a statistical power of 90% and a bilateral significance level of 5%, 25 events are needed through the follow-up period. The hazard ratio of 4 is considered conservative considering that an odds ratio of 8.6 was observed in our previous nested case-control study [8]. The expected sample size of 800 patients is considered sufficient to observe at least 25 cases of gambling disorder (primary outcome) over the follow-up period given the 3-year prevalence of PBG of 6.4% previously revealed in a similar population [8]. As for the nature and the effectiveness of treatments for PBG and/or gambling disorder, this will be documented for all patients who will have developed either the primary or secondary outcome during the study follow-up period using descriptive statistics.

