## Discussion

This prospective multicenter cohort study aims to identify potential risk factors for PBG in young adults with FEP. Among these factors, the causality of the link between the use of aripiprazole, an antipsychotic drug, and PBG, remains to be better documented, to which this prospective study will greatly contribute. Although the comorbidity of PBG and psychotic disorders has been neglected so far, it does nevertheless significantly hinder recovery of the affected individuals. For this reason, results of this study will be crucial to clinicians providing care to people with FEP. The knowledge of potential risk factors will allow them to better prevent and detect the occurrence of PBG. For instance, a better understanding of the possible association between the use of aripiprazole and PBG might ultimately influence the treatment choice through a shared-decision process, even more so in individuals at increased risk for PBG. In addition, to our knowledge, there is no screening instrument for PBG that has been specifically developed for people with FEP, which further contributes to the underestimation of this comorbidity. To this end, the procedure created for this study, which will further be refined following its completion, is expected to be spread out to all FEP programs in the province of Quebec and possibly across Canada. Such a systematic tool, in addition to information provided by the patients’ relatives, is essential for better, and earlier, detection of PBG. Treatment approaches for PBG tailored to people with psychotic disorders are still only at an embryonic phase. Thus, individuals presenting with this comorbidity are usually addressed to standard treatments that have been developed and tested for the general population. While these approaches can be hypothesized as suboptimal for people with FEP, this remains to be documented. Results of this study will hopefully raise the awareness of clinicians and researchers working in this field and serve as the basis to adapted treatments that will better support recovery.

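### The second aim sets out to demonstrate that current gambling treatments are insufficient, but an uncontrolled description of a few dozen cases, many with short follow-up, cannot show this

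*Protocol article*

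**What the plan says.** The last paragraph of the Background in the Protocol article gives the second aim: "It also aims to demonstrate that current treatments for PBG, which have not been adapted for people with FEP, are currently insufficient". The yardstick named there is recovery.

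The analysis for this aim appears in two places. Statistical analyses describes the nature and effectiveness of treatment in every patient who "developed either the primary or secondary outcome during the study follow-up period using descriptive statistics". The Abstract (Methods) says: "Descriptive statistics will document the effectiveness of treatments for problem gambling in this population". On what is recorded, Independent variables says that "the nature of the treatments received for their gambling problematic as well as their effectiveness in resolving it will be documented". The article states no comparator, benchmark rate or test for this aim.

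Elsewhere the same objective is worded neutrally. The Abstract (Background) says "to document the effectiveness of standard treatment approaches", and the Discussion says "While these approaches can be hypothesized as suboptimal for people with FEP, this remains to be documented".

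Study design fixes the calendar: admission from 1 November 2019 to 1 November 2023, assessment at admission and every 6 months, follow-up of up to 3 years, and an end date of 1 May 2024.

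**The concern.** The Background fixes the conclusion in advance, and the analysis named for it cannot deliver that conclusion.

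- To show that a treatment is insufficient, one needs either a comparison group or a recovery rate, set beforehand, below which it would be called insufficient. The article has neither.
- To blame the lack of adaptation, one would need to observe adapted treatment, and the plan compares with none.

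The calendar adds a second difficulty. Cases arise throughout follow-up, so some are observed only briefly after onset. A summary that ignores this would understate longer-term resolution.

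This matters because the Discussion expects the results to support the development of adapted treatments. A claim of insufficiency resting on this analysis would carry weight it has not earned.

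**Working it through.** **Aim against analysis.** The Background uses the language of proof. The Abstract uses the language of documentation, and the Discussion treats suboptimality as a hypothesis still open. The analysis is descriptive and fits the Abstract and Discussion, not the Background. This mismatch is visible within the article and does not depend on any unseen document.

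**Number of cases.** The article gives no figure for this aim. Its 25 events belong to the aripiprazole analysis. Inputs from Statistical analyses: 800 patients and a 3-year prevalence of 6.4%.

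- With 3 years for everyone: 800 × 0.064 = 51.2.
- With admission time *t* uniform on 0 to 4 years, follow-up is F = min(3, 4.5 − t). For t ≤ 1.5 (probability 0.375), F = 3. Otherwise (probability 0.625) F runs evenly from 3 to 0.5, with mean 1.75. E[F] = 0.375 × 3 + 0.625 × 1.75 = 2.219 years.
- Expected cases: 51.2 × 2.219 / 3 ≈ 38.

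Exact 95% intervals for about half resolved: 12/25 gives 28% to 69%, 19/38 gives 33% to 67%, and 26/51 gives 37% to 65%.

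**Observation left after onset.** Assumptions: uniform accrual, constant low hazard, no dropout, no extension of the study. The share of cases with less than *m* years left is E[min(F, m)] / E[F].

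- m = 0.5: 0.5 / 2.219 = 22.5%.
- m = 1: F is below 1 with probability 0.125 (mean 0.75 there), so E[min(F, 1)] = 0.875 + 0.125 × 0.75 = 0.969, and 0.969 / 2.219 = 43.7%.

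If onset is dated at the next 6-monthly visit, a simulation gives 24% and 45%.

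Sensitivity: suppose half of the onsets that a full 3 years would show are already present at admission. Among observed cases, the share present at admission is then 0.5 / (0.5 + 0.5 × 2.219 / 3) = 57.5%.

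- Under 6 months: 0.425 × 22.5% ≈ 10%.
- Under 12 months: 0.575 × 12.5% + 0.425 × 43.7% ≈ 26%.

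**Effect on a crude proportion, if one were used.** Take an assumed median time to resolution of 1 year (λ = ln 2), counted from onset. True resolution is then 50% at 12 months, 75% at 24 months and 87.5% at 3 years. With continuous observation, the crude proportion resolved by study end is 1 − (1 − E[e^(−λF)]) / (λE[F]).

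- E[e^(−λF)] = 0.375 × 0.125 + 0.25 × (0.7071 − 0.125) / 0.6931 = 0.2568.
- Crude proportion: 1 − 0.7432 / (0.6931 × 2.219) ≈ 52%.
- In the sensitivity case: 0.575 × (1 − 0.2568) + 0.425 × 0.517 ≈ 65%.

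So the crude figure is about 23 points below the 24-month value for incident cases, and 10 points below in the sensitivity case. It is not below the 12-month value. Reading status only at whole 6-month steps after onset would lower the 52% to about 43%. The documents do not impose that restriction, because effectiveness is taken from the medical records.

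**The case against.** The strongest reply is that only one sentence is at fault. The Abstract, Statistical analyses and Discussion already treat this as description, no test is planned, and the primary Cox analysis does not depend on it. That is right, and it limits the weight of the point. It does not remove it: the Background is where the aims are set, and no analysis detail held elsewhere would turn an uncontrolled description into a demonstration.

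A comparator is also not strictly necessary. A benchmark set in advance, with a confidence interval, could show that few patients recover. The article states none, and even that would not attribute the result to lack of adaptation.

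A reader might go further and infer that the plan uses a plain proportion that counts late cases as failures, and is therefore biased toward the conclusion it wants. The documents do not support this.

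- No section specifies a plain proportion. Descriptive statistics can include time to resolution, and such detail may sit in a full protocol or analysis plan that is not shown.
- The net direction of bias is unknown. Cut-off follow-up lowers a crude tally. Without a comparator, however, spontaneous remission would be credited to treatment, and relapse after the last visit would be missed. Both of these work the other way.
- The shortfall depends on the time point chosen, and the article names none.

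Finally, 25 cases is the plan's minimum. About 38 are expected, so an interval based on 25 overstates the imprecision somewhat.

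**Conclusion.** The concern holds for the mismatch between aim and analysis. As worded in the Background, the second aim claims a conclusion that an uncontrolled description of roughly 25 to 51 cases cannot support, and the wording conflicts with the article's own Abstract and Discussion.

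The limited follow-up is a supporting point. About 23% of incident cases would have under 6 months of observation after onset and 44% under 12 months, falling to about 10% and 26% in the sensitivity case. These shares rest on uniform accrual, constant hazard, no dropout and the stated end date. The Discussion allows the study to be extended if 25 cases have not been observed, which would change them.

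The understatement of 24-month resolution (52% against 75%) is conditional on a crude proportion being reported and on an assumed 1-year median. It illustrates a risk to avoid and is not an error found in the plan. The point should be addressed, but it concerns a secondary aim only.

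**What to change.** 1. In the Background, reword the second aim to describing the treatments received and their outcome, in line with the Abstract.
2. Report resolution among treated cases as a cumulative estimate that allows for censoring at the last assessment, with 95% confidence intervals at fixed times, for example 6 and 12 months. Use the gambling assessments already recorded and a definition of resolution set in advance by the investigators.
3. Report untreated cases separately, so that they neither dilute nor inflate the treated figure.
4. State that no inference on the sufficiency of current treatment, or on adapted against unadapted treatment, follows from these data.

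The cost is a more modest secondary aim, one simple additional analysis and no new data collection. The primary analysis is unchanged.

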## Methods

### Study design

This is a prospective multicenter cohort study with an expected sample size of 800 patients with a diagnosis of FEP, followed for up to 3 years. The recruitment is ongoing since November 1st, 2019, through November 1st, 2023. All patients admitted at the 2 study sites during this period will be evaluated for PBG by the clinical staff at admission, and every 6 months thereafter, using a screening and assessment procedure developed specifically for this study. The follow-up period will end on May 1st, 2024. During this follow-up, independent variables will be extracted from patients’ medical records by the research staff at admission, and every 6 months afterwards.

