### Dependent variables

The primary outcome is the occurrence of a DSM-5 diagnosis of gambling disorder established by the treating psychiatrist. The secondary outcome is the occurrence of PBG, as defined by a score greater than or equal to 8 on the Problem Gambling Severity Index (PGSI) [3], a reliable and validated screening instrument in general population samples which has also been used in previous studies conducted in patients with psychotic disorders [5, 7, 8]. As previously stated, these outcomes are assessed by the case managers and treating psychiatrists using a screening procedure for PBG that has been developed in collaboration with experts on gambling from the *Centre Québécois d’Excellence pour la Prévention et le Traitement du Jeu*. It is a 3-step procedure that includes (1) a screening questionnaire of gambling habits, (2) an evaluation of the severity of the gambling problematic using the PGSI, and (3) a diagnostic interview assessing the DSM-5 gambling disorder diagnosis. The first 2 steps are carried out by the patients’ case managers, while the last step is conducted by the treating psychiatrist on the basis of all available data, i.e., his or her own clinical interview, information obtained during the screening procedure, and collateral information gathered by the case manager from the patients’ relatives. Results of this procedure are recorded in the patients’ medical files and extracted by the research staff.

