The major strengths of this study include the large sample size and the length of the follow-up period, which should enable us to generate relevant findings. The population study is also representative of the FEP population of the province of Quebec, in part due to the lack of exclusion criteria and necessity to obtain consent as well as the territories served by the 2 study sites, which contain both urban and rural areas. Furthermore, the fact that no informed consent is required prevents a participation bias. Results of this study should thus be readily generalizable. In addition, the exhaustiveness and rigour of the screening and assessment procedure for PBG, as well as collateral information provided by the patients’ relatives, will ensure that the findings are reliable and less prone to detection bias. The prospective design of the study will also allow for a better examination of potential risk factors for PBG in this population and could add evidence to a possible causal link between aripiprazole use and PBG. To this end, the fact that all patients, notwithstanding the antipsychotic drugs received, will benefit from the same screening procedure for PBG will prevent a surveillance bias. The key limitations to this study are (1) previous findings regarding a possible association between PBG and aripiprazole could lead to a decrease in its use, particularly in patients deemed more at risk by clinicians, and thus introduce a prescribing bias, and (2) evaluation of the study outcomes is dependent on the cooperation of clinicians in following the PBG screening procedure. For the first point, while we have no control over the clinical practices and prescribing patterns of psychiatrists, the study will be extended if 25 cases of PBG have not been observed by the end of the recruitment period, i.e., November 1st, 2023. For the second point, a monitoring committee has been set up to closely and regularly follow up with clinicians to ensure that the screening procedure for PBG is being properly followed. Training in the use of this procedure is also provided to all new clinicians arriving during the study. Taken together, these methodological aspects will lead to results that should significantly deepen our understanding of a neglected comorbidity and hopefully positively impact services and care provided to people with FEP.

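### Gambling events are dated at detection, so the order of drug and behaviour is not secured for patients whose drug changed between onset and detection

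*Protocol article*

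**What the plan says.** All references are to the protocol article.

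- **Study design.** Patients are "evaluated for PBG by the clinical staff at admission, and every 6 months thereafter". Drug and other covariate data follow the same timetable: "independent variables will be extracted from patients’ medical records by the research staff at admission, and every 6 months afterwards".
- **Dependent variables.** "The primary outcome is the occurrence of a DSM-5 diagnosis of gambling disorder established by the treating psychiatrist". The secondary outcome is a PGSI score of 8 or more. The psychiatrist's step draws on the clinical interview, the earlier screening steps and information from relatives.
- **Independent variables.** "A patient will be considered exposed to a drug after receiving it for greater than 1 month"; for a long-acting injectable, one injection is enough. Current and past drugs are collected, "including dosages, frequency, and route of administration". Gambling before admission is "divided in 3 categories, i.e., none, occasional/recreational, or PBG".
- **Statistical analyses.** Cox models are planned for both outcomes. The sample size rests on 25 events, for an HR of 4 with aripiprazole at 90% power and two-sided 5%.
- **Background and Discussion.** The earlier study is faulted because its retrospective design could not assess causality. The present prospective design, it is said, "could add evidence to a possible causal link between aripiprazole use and PBG".

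The article names no onset date for problem gambling as part of either outcome, and gives no rule for when exposure to a drug ends.

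**The concern.** The exposure clock is finer than the event clock. Exposure can switch on after a little over a month, while the systematic look for gambling comes every six months. Two patients show what can go wrong:

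- **(a) Drug stopped in the window.** Problem gambling begins in month 2 on aripiprazole, the drug is changed in month 4, and the month-6 screen is positive. On the event date the patient is taking something else.
- **(b) Drug started in the window.** Problem gambling begins in month 2 on another drug, aripiprazole starts in month 4, and the month-6 screen is positive. On the event date the patient counts as exposed to aripiprazole, although the gambling came first.

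Coding exposure as time-dependent does not repair either case, because the event date itself is late. Nor does screening everyone alike, which the Discussion offers against surveillance bias: that equalises detection between drugs but says nothing about order within an interval. What is at stake is the advantage claimed over the earlier retrospective study, namely knowing whether drug or behaviour came first.

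**Working it through.** **1. The plan's own figure.** Schoenfeld's formula gives events = (z₀.₉₇₅ + z₀.₉₀)² / [p(1−p)(ln HR)²]. The article does not state p, the exposed share. With p = 1/3 and HR = 4: (1.960 + 1.282)² / (0.222 × 1.386²) = 10.51 / 0.427 = 24.6, so 25 events. The stated figure reproduces at about one third exposed, and that share is assumed in steps 2 to 4.

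**2. Events by true exposure at onset (assumed true HR 4).** Exposed share of events = 4 × (1/3) / [4 × (1/3) + 2/3] = 0.667. Of 25 events, 16.7 are exposed and 8.3 unexposed.

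**3. Moving cases between groups.** Person-time is held at one third and two thirds.

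- Fraction f of exposed cases moved to unexposed (patient (a), current-use rule only): HR = [(1−f) × 0.667 / 0.333] / [(0.333 + f × 0.667) / 0.667].
- Fraction g of unexposed cases moved to exposed (patient (b)): HR = [(0.667 + g × 0.333) / 0.333] / [(1−g) × 0.333 / 0.667].

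| Cases moved | Number of 25 | Calculation | HR |
|---|---|---|---|
| f = 10% | 1.7 | (0.60/0.333) / (0.40/0.667) | 3.0 |
| f = 25% | 4.2 | (0.50/0.333) / (0.50/0.667) | 2.0 |
| g = 10% | 0.8 | (0.70/0.333) / (0.30/0.667) | 4.7 |
| g = 25% | 2.1 | (0.75/0.333) / (0.25/0.667) | 6.0 |

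**4. Effect on power.** With 25 events and p = 1/3, power = Φ(√(25 × 0.222) × ln HR − 1.960) = Φ(2.357 × ln HR − 1.960). This is 90% at HR 4, 74% at HR 3 and 37% at HR 2.

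**5. Simulation under a current-use rule.** Monthly steps, onset in any month, diagnosis at the next six-monthly visit, and exposure read at that visit. Drugs are started at the rate that keeps the exposed share steady. All rates are assumptions.

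- True HR 4, exposed share 0.35 or 0.50, and 10% to 40% of users stopping per six months for reasons unrelated to gambling: about 5% to 22% of cases fall in the wrong group, the observed HR is about 3.5 to 2.1, and power at 25 events is about 85% to 44%.
- Adding an extra 10% per month stopping once gambling has begun but before diagnosis: 23% to 36% of cases are misplaced and the observed HR is about 1.6 to 1.05.
- True HR 1, exposed share 0.35: unrelated stopping leaves the HR at about 1.0, while the reactive stopping gives 0.62 to 0.67. If stopping reacts to gambling, the error is therefore bias and not only dilution.

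**6. Dependence on the exposure rule.** Under an ever-exposed rule, which the article's wording also fits, stopping moves no case, so the f rows and the downward results in step 5 do not apply. Patient (b) is misplaced under either rule: the drug has been taken for more than a month by the event date and is still being taken.

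**The case against.** A reader might infer that the study cannot establish the order of drug and gambling at all. The documents do not support that. Everyone is screened at admission and every six months, and gambling before admission is recorded. Where the drug was started before the last negative screen and continued, the order is clear. Only changes between onset and detection are ambiguous, and the article does not say how common they are. The causal claim is also modest: the study may add evidence.

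Other objections stand and narrow the point:

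- Nothing says that diagnoses are made only at scheduled visits. Ongoing case management and contact with relatives could bring detection forward.
- The downward bias needs a current-use rule that the article does not state.
- A reader might take the Discussion to predict stopping in response to gambling. It says only that use may fall in patients thought to be at risk. That is not stopping between onset and diagnosis, and it makes a start of aripiprazole in someone already gambling less likely.
- The fractions moved, the switching rates and the exposed share are assumptions.

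It can also be said that time-varying coding, lags and form fields belong in a full protocol or analysis plan that is not shown, and that charts may hold drug dates. This holds for the coding of exposure. It does not dispose of the point, because the article itself fixes the outcome definitions and the screening schedule, and no model can recover an onset date that was not collected.

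**Conclusion.** The point holds in limited form. As the article defines them, both outcomes are dated at detection, and the order of drug and behaviour is not secured for patients whose drug changed between onset and detection. A start in that window inflates the aripiprazole HR under either exposure rule. A stop moves it towards or below the null only under current use.

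The size is not known. The illustrative HRs of 3.0 to 2.0 and 6.0 rest on one third of person-time exposed, a true HR of 4 and assumed fractions moved. They are not estimates of what will happen here. They do show that with 25 events, two to four misplaced cases are enough to change the reading. The prospective design still improves on the earlier study for patients with a stable drug history. The gap is worth closing because doing so is cheap.

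**What to change.** Keep the diagnosis-dated Cox analysis as the main analysis, and add to it:

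1. At the existing third-step interview, record the estimated month of onset of problem gambling (not of first gambling), using the information from relatives already gathered. For cases already diagnosed, extract it from the chart.
2. Record drug start and stop dates, and state when exposure ends, since the direction of the error depends on it.
3. Pre-specify two sensitivity analyses for both outcomes: (i) exposure classified at the estimated onset; (ii) the event treated as lying between the last negative and the first positive screen, with exposure taken at the last negative screen.
4. Limit the causal wording if either disagrees with the main result.

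**Cost.** One onset field on the form and in the study database, drug dates where not already captured, and chart review of a few dozen cases (25 are required; 800 × 0.064 ≈ 51 would be expected if all had three years of follow-up). No visits or patients are added.

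**Downside.** Recalled onset is approximate, and clinicians aware of the aripiprazole hypothesis may date it differently around a drug start. Analysis (ii) classes as unexposed any true exposed case whose drug began after the last negative screen. Both are therefore supportive and should not replace the main analysis.
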